#### Primary outcomes

Frequency of student smoking was measured by the self-reported question: “How often do you smoke at present?” (every day; not every day, but every week; not every week, but every month; more seldom than every month; never)(ESFA) [36]. Furthermore, questions of intentions to smoke (CAS), having smoked ever (HBSC), number of cigarettes (MULD), and age at smoking initiation (HBSC) were included in the student questionnaires.

#### Distal attitudinal influences

Ethnicity was measured as student’s and parents’ country of origin and language spoken at home (HBSC) [37]. Smoking rules at home were measured by permission to smoke at home or not (X:IT).

#### Intermediate attitudinal influences

Knowledge about smoking was measured by a selection of yes/no questions about topics mentioned in the educational material (X:IT). Evaluations of consequences were measured by motives to stay smoke-free (FRI) and perceived consequences of smoking: risk, less nervousness or loneliness, ability to stay slim (ESFA). Attitudes were measured as attitudes towards rules against smoking at school and at home (CAS), and attitudes towards peers who smoke (X:IT). Parental perception of the values of the X:IT study was measured (X:IT). Parental attitudes were measured as parents’ active engagement in their child’s smoking behaviour (X:IT).

#### Distal social influences

Family structure was measured by asking whom the students live with (Pro Children). Family socioeconomic position (SEP) was measured by parental occupation (HBSC). Availability/accessibility to cigarettes from parents and peers was measured as whether cigarettes were available in the home. Also, whether the student had ever had or bought cigarettes from their parents, peers, or others (ESPAD/X:IT). Exposure to parents’ and peers’ smoking was measured by frequency measures and by asking where parents and peers smoke (HBSC).

#### Intermediate social influences

Social relations to parents and peers were measured as frequency of physical and electronic contacts as well as number and quality of confident relations (HBSC). Social norms of parents and peers were measured, as well as the student’s motivation to comply with parents’ and peers’ norms (CAS).

#### Distal intrapersonal influences

Personal factors included gender and age.

#### Intermediate intrapersonal influences

*S*elf-efficacy for smoking was measured by questions about ability to resist smoking if friends smoke, ability to explain to others if not wanting to smoke, and ability to reject smoking if offered a cigarette [38].

#### Distal environmental influences

School level SEP was measured using a question to the school coordinator regarding the wealth of the school district (HBSC). Smoking policy in the municipality and at school was measured by questions for municipal and school coordinators. Enforcement of rules at school was measured by questions for students and school coordinators (CAS).

#### Intermediate environmental influences

Availability/accessibility of tobacco at school was measured by the possibility of buying cigarettes close to the school (HBSC). Exposure at school was measured as frequency of observed smoking among teachers and other students (CAS). Both students and school coordinators answered these questions.

#### Secondary outcomes

Additional substance use, drinking alcohol, and smoking marijuana, were measured as ever use, frequency, and initiation by student self-reports (HBSC). Life satisfaction was measured by the Cantrill ladder. Well-being was measured by questions about well-being at school and in the school class, and by questions on bullying, loneliness, and frequency of symptoms (HBSC).

### Process evaluation

Questions used for process evaluation were added to the student and to the teacher questionnaires. Questions were also added to the school and municipal coordinator questionnaires at 1FU, 2FU, and 3FU. A qualitative process evaluation was conducted where quantitative evaluation was considered to be insufficient: for the recruitment of municipalities and schools into the study (conducted spring 2010), for the implementation of the smoke-free curriculum (conducted spring 2012), and for the implementation of the smoke-free dialogue (conducted autumn 2012).

The process evaluation of the X:IT study was structured according to Steckler & Linnans’ model [39]. For the overall study and for each of the three intervention components measures of ‘context,’ ‘reach,’ ‘dose delivered,’ ‘dose received,’ ‘fidelity,’ ‘implementation,’ and ‘recruitment’ were considered, developed, and measured if considered relevant. Process data were obtained from students, teachers, and coordinators at schools and in municipalities.

#### Smoke free school premises

Context was measured by questions on smoking policy at the schools and answered by students and school coordinators. The intervention was school-based and therefore, the reach included all students attending year 7 to 9. The dose received was measured by the degree to which the schools responded to the rules. These questions were answered by both students and school coordinators.

#### Smoke free contracts

Context was measured by questions regarding parental smoking behavior. Reach was measured by the proportion of students who signed a contract.

#### Smoke free curriculum

Context was measured by questions about alternative school based initiatives aiming at reducing tobacco use (school coordinators). Reach concerned all students attending year 7 to 9. The teachers who delivered the smoke free classes answered questions about how many and which mandatory and optional exercises the classes completed. The dose received is measured by students’ reports on number and quality of lessons received. Information on fidelity was also obtained from questions to the teachers. Their focus was whether the material was easy to work with, how the material performed, whether it was relevant for the students, how the students worked with the exercises, and whether the material suited the student’s age level and level of knowledge.

Overall measures on environmental circumstances were obtained by questions to municipal coordinators regarding smoking policy and further initiatives in the municipality. Information on the procedure of recruitment for the study was determined by interviewing representatives from schools and municipalities participating in or declining to the study.

### Health economic evaluation

School and municipal coordinators provided information about resources spent in connection with the study. This included time spent coordinating the study, preparing the X:IT lessons, as well as costs for lottery prizes, textbooks and other relevant material. Data provides the basis for health economic analysis of the X:IT intervention [40,41].

### Data collection

For the baseline study, data collection among students at intervention and control schools was conducted at the beginning of year 7. Follow-up data were collected at the end of year 7 (1FU), at the end of year 8 (2FU), and at the end of year 9 (3FU). We followed the students by using information on their name, birthday, class, and school. Students who changed school were omitted from the survey. Information from signed, smoke-free contracts was collected yearly. To gain information on the curricular activities, teachers were asked to complete questionnaires on conducted mandatory and optional classes. Also, we collected data among school and municipality coordinators at each follow-up (Table 2).

**Table 2 T2:** Data collection of the X:IT study – timeline, instrument and source of data

	** *Baseline* **	** *Intervention* **	** *Follow-up 1* **	** *Intervention* **	** *Follow-up 2* **	** *Intervention* **	** *Follow-up 3* **
	**September 2010**		**June 2011**		**June 2012**		**May 2013**
*Interventions schools*	Questionnaires. Students start year 7 n = 2,380		Questionnaires. Students end year 7 n = 2,202	Observation and interviews about implementation of curriculum	Questionnaires. Students end year 8 n = 1,748		Questionnaires. Students end year 9 n = 777
*Control schools*	Questionnaires. Students start year 7 n = 1,781		Questionnaires. Students end year 7 n = 1,562		Questionnaires. Students end year 8 n = 1,521		Questionnaires. Students end year 9 n = 639
*Students and parents*		Smoke free contracts n = 3,046		Smoke free contracts n = 1,731		Smoke free contracts n = 1,089	
*Study coordinator at schools*			Questionnaires n = 92		Questionnaires n = 78		Questionnaires n = 61
*Study coordinator in municipalities*			Questionnaires n = 17				Questionnaires n = 17
*Teachers at intervention schools*			Questionnaires	Interviews about implementation of curriculum	Questionnaires		Questionnaires

Students answered internet-based questionnaires in the classroom after a standardized instruction given by their teacher. The students were informed that participation was voluntary and their answers would be treated confidentially. Absentees were asked to answer questionnaires later, either at home or at school. At baseline, 4,161 students (93.1%) were included in the final data file. At first follow-up, 3,764 students were included (84.9%), and at the second follow-up, 3,269 (79.4%) were included in the data files. Due to a conflict at the Danish labor market in Spring 2013 school teachers were locked out for a month. This resulted in a response rate among students at third follow-up at only 39.4%, n = 1,416. Students were anonymized in the data file.

### Sustainability

The X:IT study is intentionally rooted in the participating municipalities to acquire sustainability. Having a municipal study coordinator, who has been following the study for years, means that the capacity is built and maintained at the municipal level and that the study can easily be implemented at other schools.

At the end of first, second, and third year of the intervention, one-day study workshops were arranged for headteachers, municipal, and school coordinators. The workshops aimed at making participants share experiences and get inspiration for new methods of teaching as well as creating an environment for discussing or solving problems that may have occurred during the intervention the previous school year. An overview of the progress of the study was also provided.

### Statistical aspects

#### Power calculations

The two Nordic studies, which the X:IT was inspired of, showed effect sizes between 30-50%. The expected effect of the intervention is a 25% lower prevalence of ‘current smokers’ (smoke daily, weekly or more seldom) at age 15 in the intervention group compared to the control group, based on what was expected to be realistic in Denmark. Other necessary assumptions for the power calculations were that each school had on average three year 7 classes with an estimated average of 20 students per class. Within schools, students’ smoking behavior is related. To estimate the intraclass correlation (0.053 for smoking weekly or more often among year 9 students), we used data from a large, nationally representative study among 15-year olds with similar measures and design, “Health Behaviour in School-aged Children 2006” (HBSC) [42]. Using these assumptions and a power of 80%, we needed 46 intervention schools and 46 control schools. Power calculations were conducted according to Donner & Klar, [43].

#### Data process and analyses

Baseline data were imported into SAS version 9.2. Information from smoke-free contracts was merged with the baseline data. Variables on ethnic background were categorized into ethnic Danish, immigrants, and descendents of immigrants according to the definitions by Statistics Denmark. Variables on parental occupation were coded into six groups according to the Danish National Institute of Social Research: social class I (high) to V (low) and a group VI covering parents who were living on social welfare benefits. The students were categorized, according to the highest ranking parent, into three groups, family SEP I-II (high), III-IV (medium), and V-VI (low).

Future analyses of first follow-up data will be conducted by means of multilevel logistic regression models. Furthermore, available case and intention-to-treat analyses will be performed; the latter with multiple imputation of missing data. In the analysis of second follow-up, a mixed model with repeated measures will be used. The random effects will handle the covariance within schools and classes. The fixed effects will include an interaction between time and the intervention indicator.

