### Descriptive analyses of baseline data

Ninety-seven schools from 17 municipalities entered random allocation. After allocation, three schools withdrew from the study leaving 51 schools as intervention schools and 43 schools as control schools. At baseline in September 2010, 4,468 year 7 students were eligible, of which 4,167 answered the baseline questionnaire (response rate = 93.3%). We had to exclude six questionnaires due to sabotage, leaving 4,161 students in the final data file. Intervention schools and control schools did not differ by average number of year 7 students per school. Further, there were no differences in the gender composition or the composition of ethnic background, own smoking status or whether smoking control was enforced at school premises (Table 3). In the control group, more students were from high socioeconomic position compared to the intervention group, whereas, students from lower SEP families were equally distributed. More students at control schools saw teachers smoke daily and more parents in the intervention group were daily smokers. More students from intervention schools answered correctly to questions regarding knowledge of smoking and tobacco (Table 3).

**Table 3 T3:** Description of the intervention and control group at baseline in the X:IT study

	** *Intervention group* **	** *Control group* **
*Background factors*		
Number of schools (%)	51 (54.3%)	43 (45.7%)
Number of students (%)	2380 (57.2%)	1781 (42.8%)
Average number of students pr. school	49.6	45.0
Sex (boys) (E)	50.8%	51.3%
Ethnic background (A)		
• Danes	93.0%	92.8%
• Descendants	4.1%	4.2%
• Immigrants	2.9%	3.1%
Family socioeconomic position (SEP) (C)		
• High	33.6%	38.7%
• Medium	48.4%	42.8%
• Low	18.0%	18.5%
*Intermediate factors: individual*		
At least 7 out of 13 right answers on knowledge questions (B)	60.1%	54.2%
Students should be allowed to smoke outdoors on school premises (B)	12.8%	13.8%
Difficult to stay smoke-free if friends smoke (F)	59.9%	60.2%
Willing to comply with parental nonsmoking norms (D)	90.7%	90.0%
*Intermediate factors: context*		
Allowed to smoke at home (A)	4.7%	4.1%
Parents daily smokers (C)		
• Male	31.1%	27.9%
• Female	28.7%	24.3%
Best friend smokes (C)	6.9%	8.3%
Teachers control smoking (G)		
• Daily	6.4%	6.0%
• Sometimes	27.7%	25.2%
• Don’t know	47.1%	49.3
See teachers smoke (H)		
• Daily	17.2%	20.5%
• Sometimes	43.4%	43.1%
*Outcome*		
Have ever tried smoking	17.4%	19.2%
Monthly smokers	3.0%	4.2%

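### The only effect term named for second follow-up is a time-by-intervention interaction, which, read as change from baseline, subtracts the whole chance baseline gap and costs precision against the between-arm contrast used for sizing

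*Protocol article*

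**What the plan says.** Under Power calculations, the protocol article defines the effect as a between-arm contrast at one age: "The expected effect of the intervention is a 25% lower prevalence of ‘current smokers’ (smoke daily, weekly or more seldom) at age 15", "at age 15 in the intervention group compared to the control group" being the comparison that is sized. No change from baseline enters that calculation, which ends at 46 schools per arm: "Using these assumptions and a power of 80%, we needed 46 intervention schools and 46 control schools".

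Under Data process and analyses, the model differs by wave. For the first wave: "Future analyses of first follow-up data will be conducted by means of multilevel logistic regression models". For second follow-up, the article moves to a repeated-measures mixed model with random effects for schools and classes, and the only effect term it names is this: "The fixed effects will include an interaction between time and the intervention indicator". It does not say which contrast from that model is the intervention effect, how time is coded, or which link is used.

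Table 3, under Descriptive analyses of baseline data, gives the row "Monthly smokers" as 3.0% in intervention schools and 4.2% in control schools.

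**The concern.** With baseline as the reference time and a logit link, a time-by-intervention coefficient equals the follow-up log odds ratio minus the baseline log odds ratio. That is not the contrast on which the trial was sized. The baseline outcome is rare, so its log odds ratio is imprecise. Because schools were allocated by lot, the baseline gap carries no information about the intervention. Part of it does predict later smoking, and removing that part is useful. The interaction removes all of it, so the rest enters the estimate as noise.

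The observed gap favours intervention schools (3.0/4.2 = 0.714, or 29% lower). Full subtraction would therefore pull the estimated effect towards no effect. Second follow-up matters because it is the latest wave with a good response (79.4%, against 39.4% at third follow-up).

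**Working it through.** **1. The sizing is a cross-sectional contrast.** The inputs are 60 students per school ("each school had on average three year 7 classes with an estimated average of 20 students per class"), an "intraclass correlation (0.053 for smoking weekly or more often among year 9 students"), power 80% and a prevalence ratio of 0.75. Two-sided 5% is assumed. The control prevalence is not stated. The design effect is 1 + 59 × 0.053 = 4.127. At a control prevalence of 25.5%, the two-proportion formula gives 669 students per arm, and 669 × 4.127 / 60 = 46.0 schools. The stated 46 is thus reproduced with no baseline term.

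**2. Baseline gap.** OR = (0.030/0.970)/(0.042/0.958) = 0.705, so d0 = ln 0.705 = −0.349. With the sizing intraclass correlation of 0.053 applied at baseline, the approximate 95% CI is 0.39 to 1.28, which is compatible with chance.

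**3. Formulas.** Let d0 and d2 be the log odds ratios at baseline and second follow-up, V0 and V2 their variances, and r their correlation.
- Interaction: d2 − d0, with variance Vi = V0 + V2 − 2r√(V0·V2).
- Common baseline mean: d2 − b·d0, with b = r√(V2/V0) and variance Vc = V2(1 − r²).
- Vi = Vc + (1 − b)²·V0, so the loss disappears only if b = 1.

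**4. One worked case.** The counts come from Tables 2 and 3: 2,380 and 1,781 students at baseline, 1,748 and 1,521 at second follow-up, in 51 and 43 schools. Assumed: control prevalence 15%, true ratio 0.75, intraclass correlation 0.02 at baseline and 0.053 at follow-up, r = 0.3.
- V0 = 1.913/(2380 × 0.030 × 0.970) + 1.808/(1781 × 0.042 × 0.958) = 0.0276 + 0.0252 = 0.0529 (unrounded sum).
- V2 = 2.764/(1748 × 0.1125 × 0.8875) + 2.822/(1521 × 0.15 × 0.85) = 0.0158 + 0.0146 = 0.0304.
- Vi = 0.0529 + 0.0304 − 0.6 × √(0.0529 × 0.0304) = 0.0592.
- Vc = 0.0304 × 0.91 = 0.0277, so the variance ratio is 2.1.
- True follow-up log OR = ln 0.718 = −0.331. Power is 27% for the interaction and 51% for the constrained contrast. Ignoring baseline altogether (variance 0.0304) gives 48%.

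**5. Range.** The same formulas were run over control prevalence 12-20%, baseline intraclass correlation 0 to 0.053 and r from 0.2 to 0.6:

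| Quantity | Interaction | Common baseline mean |
|---|---|---|
| Variance ratio | 1.1 to 4.3 | 1 |
| Power for a true 25% reduction | 16-67% | 40-80% |

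A separate simulation under the null gave rejection rates of 0.049 (interaction) and 0.047 (constrained), so both hold their level.

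**6. Expected interaction, given the observed baseline gap.** E(d2 | d0) = δ + b·d0, where δ is the true log OR. The expected interaction is therefore δ + (b − 1)·d0. In the worked case b = 0.3 × √(0.0304/0.0529) = 0.227. The expected follow-up OR is exp(−0.331 − 0.227 × 0.349) = 0.664, and the interaction OR is 0.664/0.705 = 0.94. Over the range in step 5 it runs from 0.81 to 0.98.

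**7. When it is about 1.0.** If the observed follow-up prevalence ratio is exactly 0.75, the follow-up OR is 0.730, 0.718, 0.706 or 0.695 at control prevalences of 10%, 15%, 20% or 24%. Dividing by 0.705 gives 1.03, 1.02, 1.00 or 0.99.

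**The case against.** The strongest reply is that the sentence says what the model contains, not what will be tested. A repeated-measures model needs a time-by-arm term to give an arm contrast at each wave, and the remedy proposed here contains such terms too. The follow-up contrast could be derived from the planned model. This stands: the article does not make the interaction the deciding test. But it is the only effect term named, and its ordinary reading is change from baseline.

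A second reply is that choosing the reported contrast belongs in a statistical analysis plan, which is not at hand. That is fair for time coding or baseline constraints, and it is why the point is not raised as an omission. The point is that the one term the article does name is a less efficient choice than another available from the same data.

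Third, the occasions differ. The sizing is at age 15, whereas the model is for the end of year 8. This also stands, and it means the two sections do not strictly contradict each other.

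A reader might infer that a trial meeting its target would show nothing on the interaction. The documents do not support that. An OR near 1.0 needs an observed follow-up ratio of exactly 0.75. If intervention schools began lower by chance and smoking is correlated over time, a true 25% effect predicts an observed ratio below 0.75.

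The figures also depend on the outcome and the scale. Using the other outcome row in Table 3, ever tried (17.4% v 19.2%, OR 0.887), and an observed ratio of exactly 0.75, the interaction OR is 0.82 to 0.78 at control prevalences of 10-24%. On the risk-difference scale, with monthly smoking, the interaction is −2.6 to −5.3 percentage points at 15-26%. Adding a student-level random intercept (assumed SD 1 to 3) gives 0.81 to 0.95 at 24-26%.

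**Conclusion.** The point holds as one of efficiency and clarity. The effect named for second follow-up is not the kind of contrast used for sizing. If it is used as change from baseline on the logit scale, it subtracts a baseline gap compatible with chance in full. Validity is not at issue, because the test keeps its level. The cost is a variance about 1.1 to 4.3 times that of a baseline-constrained contrast and, given the observed gap, an expected interaction OR of roughly 0.81 to 0.98 under a true 25% reduction.

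These figures rest on monthly smoking as a proxy for current smoking (Table 3 does not give the latter), a logit link, and assumed baseline intraclass correlations, correlations over time and control prevalences of 12-20%. They also ignore stratification by municipality. The documents do not support saying that the analysis would miss a fully achieved target, or that the two contrasts must lead to opposite conclusions. This is a cheap improvement.

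**What to change.** In Data process and analyses, state that the effect at second follow-up is intervention v control at that follow-up. Estimate it in one of two ways:

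- from the planned repeated-measures model, with time categorical and a common baseline mean in both arms; or
- from a multilevel logistic model of smoking at second follow-up, adjusted for baseline smoking.

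Report the change-from-baseline interaction only as a sensitivity analysis.

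The cost is one or two sentences, with no new data. The small downside is that a common baseline mean relies on randomisation having been carried out properly.
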